**Figure 4. The dose adjustment plan for IFN- $\gamma$  for cohort 1.**

- Schedule of IFN- $\gamma$  and dose adjustment for cohort 2 (Figure 5)
- 1) The initial dose of IFN- $\gamma$
- a. The first dose of IFN- $\gamma$  100 mcg will be administered on day 0 in the clinic.
  - b. The subject will continue self-injection of 100mcg, three times a week for two weeks (e.g., Monday, Wednesday, Friday or Tuesday, Thursday, Saturday)

- 2) 48 hours after the initial dose of IFN- $\gamma$  (up to 1 week)
  - a. Bone marrow aspirate (no biopsy) will be performed for morphology, flow cytometry, and a research sample. (Cytogenetics/molecular testing only needed if clinically indicated to follow MRD.)
- 3) One week after the initial dose of IFN- $\gamma$  (window: - 3 days to + 7 days)
  - a. Subjects tolerating 100 mcg three times a week can proceed to DLI if eligible.
  - b. If the subject is not tolerating a given dose, it can be decreased to 100mcg two times a week for one week (+/- 5 days). If tolerated, the patient would then be eligible to proceed to the DLI phase.
  - c. If 100 mcg two times per week is not tolerated, IFN- $\gamma$  will be discontinued, and the subject will be withdrawn from further on-study treatment. The subject may still proceed to DLI off study.

[figure not shown]

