#### 6.4.2.2 For the subjects for whom donor leukocytes are available (cohort 2)

- After the first dose of DLI, the same dose of IFN- $\gamma$  as used pre-DLI for that patient will be continued three times a week for four weeks. If the subject develops intolerance to IFN- $\gamma$  during this period, we will reduce the frequency of IFN- $\gamma$  to once weekly.
- A minimum of four weeks after the first dose of DLI, the subject will receive the second DLI, in the absence of active grade II-IV GVHD or de novo grade III-IV, or progressive chronic GVHD requiring new systemic treatment or increased doses of current systemic treatment per treating physician's determination. IFN- $\gamma$  will be continued at the same dose three times weekly. There is an optional bone marrow aspirate if clinically indicated prior to the second DLI per the treating physician, and a research sample can be collected at that time.
- 8 weeks after the first dose of IFN- $\gamma$  (or approximately 7 weeks after the first dose of DLI), the frequency of IFN- $\gamma$  will be tapered to once weekly, continued until the next DLI.
- A minimum of 4 weeks after the second DLI, the subject will receive the third dose of DLI, in the absence of active grade II-IV GVHD or de novo grade III-IV, or progressive chronic GVHD defined by a requirement for new systemic treatment or increased doses of current systemic treatment. IFN- $\gamma$  will be continued at the same dose once weekly for three more weeks. There is an optional bone marrow aspirate if clinically indicated before the third DLI, and a research sample may also be collected at that time.
- IFN- $\gamma$  will be continued once weekly until four weeks of the last dose of DLI or 12 weeks after the first dose of IFN- $\gamma$  whichever occurs later. If the subject develops intolerance to IFN- $\gamma$  during this period, we will discontinue IFN- $\gamma$
- At the end IFN- $\gamma$  treatment, the bone marrow aspirate is required ideally within seven days after the last dose of IFN- $\gamma$

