- Optional bone marrow aspirates (no biopsy) will be performed for morphology, flow cytometry, and research sample (10ml) if clinically indicated. Cytogenetics/molecular testing only needed if clinically indicated to follow MRD if clinically indicated.
- If the second or third dose of DLI is available, the DLI will be infused at minimal 4 weeks of interval in the absence of active grade II-IV GVHD or de novo grade III-IV, or progressive chronic GVHD requiring new treatment or increased doses of current treatment per treating physician's determination.
- There is an optional bone marrow aspirate if clinically indicated before the second or the third DLI per the treating physician, and research sample (10mL in green top heparin tube) will be collected.

6.5.2.7 Protocol visit #6: Stage 2 follow up safety assessment, 56 days (+/- 7 days) after the first dose of IFN- $\gamma$  (= approximately 49 days +/- 7 days after the first DLI or 21 days +/- 7 days after the second DLI)

- Clinical safety monitoring: Any reaction or symptoms related to the IFN- $\gamma$  or DLI will be assessed, specifically focusing on active grade II-IV GVHD or de novo grade III-IV, or progressive chronic GVHD
- Laboratory monitoring: CBC with differential, chemistry panel (Na, K, Cl, CO2, creatinine, glucose, urea nitrogen, phosphorus, magnesium, albumin, calcium, LDH, uric acid), hepatic (alkaline phosphatase, ALT, AST, and total bilirubin) panel
- Research sample collection: 30 mL of peripheral blood (10 mL green top heparin tube x 3 tubes) will be collected.
- Optional bone marrow aspirates (no biopsy) will be performed for morphology, flow cytometry, and research sample (10ml) if clinically indicated. Cytogenetics/molecular testing only needed if clinically indicated to follow MRD if clinically indicated.
- If the third dose of DLI is available, the DLI will be infused at minimal 4 weeks of interval in the absence of active grade II-IV GVHD or de novo grade III-IV, or progressive chronic GVHD requiring new treatment or increased doses of current treatment per treating physician's determination.
- There is an optional bone marrow aspirate if clinically indicated before the third DLI per the treating physician, and research sample (10mL in green top heparin tube) will be collected.

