| Donor lymphocyte infusion                                                                          |           |         |    |      | X       |      | X*2) | X*3) |      |       |
| Research sample collection                                                                         |           |         |    |      |         |      |      |      |      |       |
| Bone marrow aspirate (10mL)                                                                        | X*1)      | X*1)    | X  |      | X       |      |      | X    |      | X*4)  |
| Peripheral blood (30ml)                                                                            |           | X       | X  |      | X       |      | X    | X    | X    | X     |
| *1) No need to repeat bone marrow if the research sample was collected during the screening period |           |         |    |      |         |      |      |      |      |       |
| *2) Only applicable if the second dose of DLI is feasible                                          |           |         |    |      |         |      |      |      |      |       |
| *3) Only applicable if the third dose of DLI is feasible                                           |           |         |    |      |         |      |      |      |      |       |
| *4) This bone marrow is optional and can be collected if clinically indicated.                     |           |         |    |      |         |      |      |      |      |       |

## 15.4 Appendix D. Schedule of event for cohort 2

|                                                                                                    | Screening | Stage 1 |    | Stage 2  |      |      |      |       |       |       |
|----------------------------------------------------------------------------------------------------|-----------|---------|----|----------|------|------|------|-------|-------|-------|
| Visit                                                                                              | Pre       | V1      | V2 | V3       | V4   | V5   | V6   | V7    | V8    | V9    |
| Days                                                                                               | -14 to -1 | 0       | 2  | 7        | 21   | 35   | 56   | 84    | 112   | 180   |
| Window (days)                                                                                      |           |         | +5 | -3 to +5 | +/-5 | +/-5 | +/-7 | +/-14 | +/-14 | +/-28 |

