| History and physical exam                                                                          |           | X       | X  | X        | X    | X    | X    | X     | X     | X     |
| CBC, chemistry, and hepatic panel                                                                  |           |         |    | X        | X    | X    | X    | X     | X     | X     |
| Bone marrow examination                                                                            |           | X*1)    | X  |          |      |      |      | X     |       | X     |
| STR chimerism                                                                                      |           | X       |    |          |      | X    |      | X     |       | X     |
| Treatment                                                                                          |           |         |    |          |      |      |      |       |       |       |
| IFN-γ (Actimmune) per protocol                                                                     |           | X       | X  | X        | X    | X    | X    |       |       |       |
| Donor lymphocyte infusion                                                                          |           |         |    | X        |      | X*2) | X*3) |       |       |       |
| Research sample collection                                                                         |           |         |    |          |      |      |      |       |       |       |
| Bone marrow aspirate (10mL)                                                                        | X*1)      | X*1)    | X  |          |      | X*4) | X*4) | X     |       | X*4)  |
| Peripheral blood (30ml)                                                                            |           | X       | X  |          |      | X    | X    | X     | X     | X     |
| *1) No need to repeat bone marrow if the research sample was collected during the screening period |           |         |    |          |      |      |      |       |       |       |
| *2) Only applicable if the second dose of DLI is feasible                                          |           |         |    |          |      |      |      |       |       |       |
| *3) Only applicable if the third dose of DLI is feasible                                           |           |         |    |          |      |      |      |       |       |       |

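### Appendix D marks cohort 2's third DLI at day 56, 21 days after the second, although the protocol requires at least four weeks between infusions

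*Protocol*

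**What the plan says.** Appendix D (section 15.4) is the schedule of events for cohort 2. Its day row, read from V4 to V9, is "21 | 35 | 56 | 84 | 112 | 180", and V3 is day 7. The donor lymphocyte infusion row carries a mark at V3, a mark with footnote 2 at V5 (day 35), and a mark with footnote 3 at V6 (day 56). Footnote 3 reads "3) Only applicable if the third dose of DLI is feasible".

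The body text gives the interval rule three times for this cohort:

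- Section 6.4.2.2: "A minimum of 4 weeks after the second DLI, the subject will receive the third dose of DLI".
- Section 6.5.2.6 (V5): "If the second or third dose of DLI is available, the DLI will be infused at minimal 4 weeks of interval".
- Section 6.5.2.7 (V6): "If the third dose of DLI is available, the DLI will be infused at minimal 4 weeks of interval".

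The heading of 6.5.2.7 also places V6 relative to the earlier infusions: "approximately 49 days +/- 7 days after the first DLI or 21 days +/- 7 days after the second DLI".

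**The concern.** The table and the text disagree on when the third infusion may be given. Read alone, the table puts it three weeks after the second and makes it depend only on feasibility.

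The interval is the period in which GVHD after one infusion can appear before the next, larger one is given. Table 3 sets the second DLI at 1 × 10^7 CD3+ cells/kg. The third may be up to 1 × 10^8 for a matched sibling donor or 5 × 10^7 for a matched unrelated donor, so up to 10 or 5 times the second dose. Section 2.2 names GVHD as the main safety concern, and section 9.2.3 lists acute GVHD after DLI at up to 61%. Infusing on day 56 after a day 35 infusion would shorten that observation by a week and would be a protocol deviation that the schedule itself had suggested.

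**Working it through.** **Inputs.** From Appendix D: V3 day 7, V5 day 35 ± 5, V6 day 56 ± 7, V7 day 84. From 6.4.2.2: at least 28 days from the first DLI to the second, and at least 28 from the second to the third. From 6.3.2: the stage 1 assessment one week after the first dose has "window: - 3 days to + 7 days". From 6.5.2.4: V3 is day 7, −3 to +5 days, and the first DLI may follow within two weeks.

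**1. Nominal gaps in Appendix D.**
- First to second DLI: 35 − 7 = 28 days, which meets the minimum.
- Second to third DLI: 56 − 35 = 21 days, which is 28 − 21 = 7 days short.

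**2. Check against the text.** The 6.5.2.7 heading gives the same 21 days, so the gap does not come from misreading table columns. Its window runs from 21 − 7 = 14 to 21 + 7 = 28 days after the second DLI. Only the last day satisfies the rule stated in that same section.

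**3. Earliest compliant third DLI** = day of first DLI + 28 + 28.
- First DLI on day 7: 7 + 56 = day 63.
- First DLI on day 7 − 3 = 4, the early edge in both 6.3.2 and 6.5.2.4: 4 + 56 = day 60.

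The V6 window is 56 − 7 = day 49 to 56 + 7 = day 63. At most days 60 to 63 of it can be compliant, and only if the first DLI is given by day 63 − 56 = 7. Day 56 itself never is.

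**4. Later first DLI.** An assessment at day 7 + 7 = 14 (6.3.2), with the first DLI two weeks later on day 28, gives 28 + 56 = day 84, which is V7. This is an example, not an upper limit. A patient not tolerating the dose has a further option, "it can be decreased to 100mcg two times a week for one week (+/- 5 days"), which can push the date later still.

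**5. Comparison with cohort 1.** Appendix C marks DLI on days 28, 56 and 84: 56 − 28 = 28 and 84 − 56 = 28. The same footnote wording does no harm there because the marks are correctly spaced. The conflict is specific to cohort 2.

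**6. Where the text seems to put the third DLI.** Section 6.4.2.2 continues weekly IFN-γ for three weeks after the third DLI. Counting back from the 12-week end of treatment, 84 − 21 = day 63, which equals 35 + 28. This is inference, but it suggests the intended date is day 63.

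**The case against.** The strongest reply is that the governing rule is clear and appears where it is needed. A site working through V6 under 6.5.2.7 reads both the four-week interval and the GVHD conditions in that visit's own instructions. A mark in the table also need not be an infusion date: the first DLI is marked at V3 but may be given up to two weeks after it. On that reading V6 is simply the last visit before a day 63 infusion, and day 63 is inside the V6 window. None of the DLI footnotes in either appendix carries the interval, so faulting this one may look like preference. No endpoint depends on it either: the main biological comparison uses the marrow taken before treatment and at V2, and the cohort 2 target in 8.2.1 counts patients with at least one DLI.

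Most of this stands as a limit on size. The safeguard is not lost, and the primary analysis is unaffected. It does not remove the contradiction. The schedule works only on the last days of the V6 window, and only when the first DLI is given by day 7. Footnote 3 differs from the others because its mark is the only one placed at a non-compliant gap. The three-week IFN-γ sentence, which can be cited in the schedule's defence, points to day 63 and so supports the view that the day 56 mark is misplaced.

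**Conclusion.** The point holds. The third-DLI mark in Appendix D is 7 days earlier than the protocol's own minimum allows on the nominal calendar, and no permitted timing of the first DLI makes day 56 compliant. The defect is confined to that mark and its footnote; the body text is consistent.

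The consequence is a risk of a shortened interval, 21 days instead of at least 28, before the highest permitted cell dose. It would arise only if a site scheduled from the table without applying 6.5.2.7. Few patients could be affected: 8.2.1 anticipates up to six in cohort 2, and a third DLI depends on availability, on GVHD status and on the treating physician. The conclusion assumes that four weeks means 28 days and that the first DLI is not given before the day 4 edge of the assessment window. It is worth correcting because this is a wrong day in a current treatment schedule and the correction is nearly free.

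**What to change.** Keep the four-week minimum and amend footnote 3 of Appendix D to say: *only if the third dose is feasible, and not before 28 days after the actual date of the second DLI*. Moving the mark to between V6 and V7 would also work, but it needs a new column and would still be wrong for patients whose second DLI is late. The footnote follows the actual date, so it is the better choice. Section 6.5.2.7 needs no new sentence.

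Where the third DLI then falls between numbered visits, GVHD should be assessed on the day of infusion, so that the existing condition on GVHD is checked when it applies.

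The cost is one footnote and, for the few patients concerned, one GVHD check. No extra patients are needed, and the endpoints and analysis do not change.
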